### Data management

The data-coordinating center in Severance Hospital is collecting data through a secure Internet connection to the central server and monitoring the overall dataset. At the start of the trial, the monitors conducted a tutorial on the web-based data entry system and the image upload system. They will audit the overall quality and integrity of the data regularly every 6 months and, if necessary, contact the site investigator and coordinator to review and confirm the correctness of the data with source data in compliance with the protocol. The monitors will verify that all adverse events were documented in the correct format and are consistent with protocol definition. The monitor conducts the monitoring procedure independently from the investigators and the sponsor. The primary and secondary endpoints in this trial include only the image quality and not the patients’ clinical outcomes. If the quality is not enough to determine significant coronary artery disease due to insufficient enhancement from a low-concentration contrast agent, repeat examination with a high-concentration contrast agent can be used at the site investigator’s discretion. Therefore, the conduct of an interim analysis is not needed to evaluate any potentially important reasons to modify or discontinue the trial. Adverse effects and serious adverse events will be recorded in the case report form. A summary of adverse effects and serious adverse effects will be immediately forwarded the independent Institutional Review Board and local health authorities, according to local regulations.

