### Efficacy analysis

#### Primary efficacy analysis

The primary efficacy measurement is the HU value of the coronary arterial lumen acquired from the comparison of the image quality from the three different protocols of contrast media in coronary CT angiography. The coronary artery is divided into 17 segments according to the modified American Heart Association (AHA) classification, and luminal enhancement is measured for each segment with avoidance of the borderline between the lumen and the vessel wall or epicardial tissue, artifacts, or calcification. Measurement is performed on three different points in each segment and the average value is used for the HU value of each segment. The mean HU value of left main artery and proximal right coronary artery will be compared between the different arms of the trial.

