### Statistical methods

#### Sample size and power calculation

The noninferiority margin was justified by an indirect confidence interval approach using the point estimate because the constancy assumption was not applicable in this trial. In a previous study [11], the reduction rate between iopamidol 370 mgI/ml and iodixanol 320 mgI/ml was 18 % (from 439.96 to 362.06 HU), and we assumed that the HU value between the low-concentration and high-concentration groups would be the same. Consequently, we estimate 9 % (0.5 × (18 % - 0 %)) of the reported mean HU [10] to be the noninferiority margin, allowing a loss of less than 50 % of the active control effect, which corresponds to a noninferiority margin of 51.26 HU [12]. Clinically, 250–300 HU is considered sufficient enhancement for coronary angiography [13]. Therefore, a reduction of 51.26 HU from 439.96 HU, which results in 388.7 HU, is clinically acceptable. For the mean contrast enhancement as an attenuation value of CT (HU) in the noninferiority test, we assumed same mean HU among the three groups and a standard deviation of 118.93 for the HU based on a previous study [10]. With these assumptions and a 10 % dropout rate, 106 subjects per group are needed to obtain 80 % statistical power with a corrected two-sided α ≒ 0.0167 (=0.05/3).

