#### Primary statistical analysis

Per-protocol analysis will be performed primarily; an additional intention-to-treat analysis will be also performed. The 98.33 % confidence interval (CI) for the difference of mean contrast enhancement in the ROIs will be calculated. The noninferiority of the low-dose group compared to the high-dose group will be demonstrated if the lower bound of the two-sided 98.33 % CI lies above the pre-specified noninferiority margin. Because missing values are expected for 5 % or fewer of the participants, we have planned complete-case analysis for the primary analysis. To account for multiple observations per patient in secondary analysis, we will use a linear mixed model, including fixed effects for the group and random intercepts for the patient. Patients with a missing observation in some vessel or segment will be included in the per-vessel and per-segment analysis by using the linear mixed model. Analysis of covariance (ANCOVA) with BMI as a covariate will be used to compare the mean HU of the myocardium on static perfusion CT. Inter-reader agreement for the assessment of image quality will be evaluated using a linearly weighted kappa statistic. Analysis of variance (ANOVA) will be used to compare mean changes in heart rate before and after CT examinations among the three groups. To compare the diagnostic accuracy of invasive coronary angiography for diagnosis of significant coronary artery stenosis with more than 50 % stenosis among the three groups, logistic regression analysis using a generalized estimating equation (GEE) will be used to account for the correlation among multiple segments within the same subject. All statistical analyses will be performed using SAS (SAS Ver. 9.2; SAS Institute, Cary, NC, USA) and two-sided *P* values less than 0.05 will be considered statistically significant.

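### The plan allows an outcome-triggered repeat scan with the comparator agent, worded for low-concentration scans only, but does not fix the first randomised scan as the source of the primary HU in a noninferiority decision that rests on the per-protocol set

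*Protocol article*

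**What the plan says.** - **Repeat rule (Data management).** If image quality does not allow a reading "due to insufficient enhancement from a low-concentration contrast agent", a "repeat examination with a high-concentration contrast agent can be used at the site" investigator's discretion. The rule is worded for the low-concentration agents only. The article cites it as a reason for having no interim analysis and does not connect it to the handling of data.
- **Endpoint (Primary efficacy analysis).** The primary measurement is coronary luminal HU: "The mean HU value of left main artery and proximal right coronary artery will be compared between the different arms of the trial".
- **Blinding (Trial design; Randomization).** Subjects and the outcome assessor are blinded. Investigators, coordinators and CT operators are named as people who can disclose the agent used.
- **Analysis set (Primary statistical analysis).** "Per-protocol analysis will be performed primarily; an additional intention-to-treat analysis will be also performed". The article gives no definition of the per-protocol set.
- **Decision rule (same section).** Noninferiority is shown "if the lower bound of the two-sided 98.33 % CI lies above the pre-specified noninferiority margin". The Sample size section derives a 9% reduction, "which corresponds to a noninferiority margin of 51.26 HU". No role in this rule is given to the intention-to-treat result.

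**The concern.** Three features combine badly. A repeat follows from a poor value of the quantity under test. It can arise only in the arms whose noninferiority is to be shown. The person who orders it may know the allocation.

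In that setting the noninferiority decision rests on a per-protocol set, the kind of set from which patients who leave their assigned treatment are ordinarily removed. If an examination with the comparator agent counted as leaving the protocol, the failures of the low-concentration agents would drop out of the primary comparison. If the repeat images supplied the HU instead, comparator enhancement would be credited to the low-concentration arm. An intention-to-treat analysis using those images would then give no protection.

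Both routes act in one direction, toward a noninferiority claim. Neither could be repaired credibly once results by arm are known.

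**Working it through.** **Inputs.** From Sample size and power calculation: SD 118.93 HU, margin 51.26 HU, true difference 0, 80% power, 10% dropout, 106 per group. From Primary statistical analysis: two-sided 98.33% CI, so one-sided 0.05/6 = 0.00833 per comparison and z = 2.394. The share of patients affected, q, is not in the document and is varied as an assumption.

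**The plan's own figure.** n = 2 × SD² × (z_α + z_β)² / margin². With one-sided α = 0.0167 (z = 2.128) and z_β = 0.842:

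2 × 118.93² × (2.128 + 0.842)² / 51.26² = 95 after rounding up; 95/0.9 = 105.6, so 106.

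This matches the stated 106 and gives 95 evaluable per arm. With the one-sided 0.00833 implied by the 98.33% interval, the same formula gives 113, or 126 after dropout. That mismatch is a separate matter; here it only explains why 95 and z = 2.394 appear together.

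**If nothing is removed.** SE = 118.93 × √(2/95) = 17.26 HU. When the true deficit equals the margin, the chance of declaring noninferiority is 0.83%.

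**If the lowest share q of one low-concentration arm is dropped.** With z_q the standard normal q-quantile and φ the normal density, the mean shift is SD × φ(z_q)/(1 − q). For q = 0.05: 118.93 × 0.1031/0.95 = 12.9 HU, and 12.9/51.26 = 25% of the margin. The truncated arm has SD about 107.0 and 90.25 patients, so SE = √(118.93²/95 + 107.0²/90.25) = 16.6 HU. The error at the margin is the upper normal tail beyond 2.394 − 12.9/16.6 = 1.617, which is 5.3%.

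**If those values are replaced by values with the high-arm mean.** The shift is q × 51.26 + SD × φ(z_q), with SE held at 17.26 HU. For q = 0.05: 2.6 + 12.3 = 14.8 HU after rounding.

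| q (assumed) | Dropped: shift | Error at margin | Replaced: shift | Error at margin |
|---|---|---|---|---|
| 1% | +3.2 HU | 1.4% | +3.7 HU | 1.5% |
| 2% | +5.9 HU | 2.0% | +6.8 HU | 2.3% |
| 3% | +8.3 HU | 2.9% | +9.6 HU | 3.3% |
| 5% | +12.9 HU | 5.3% | +14.8 HU | 6.2% |
| 10% | +23.2 HU | 16.5% | +26.0 HU | 18.7% |

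**What share could be affected?** The Sample size section cites 250–300 HU as sufficient. Take 250 HU as an illustrative cut-off.

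- Low-arm mean 439.96 − 51.26 = 388.7 HU: (250 − 388.7)/118.93 = −1.17, so about 12% fall below. If all are affected, the shift is +27 HU (dropped) or +30 HU (replaced) and the error 24% to 26%. If half of them are dropped, the shift is about +13 HU and the error about 5%.
- High-arm mean back-calculated from the margin as 51.26/0.09 = 569.6 HU (an assumption): at a 51.26 HU deficit only about 1.2% fall below 250 HU. The shift is about +4 HU and the error about 1.5%.

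**If the first scan is always analysed,** the shift from this source is 0 HU and the error stays at 0.83%.

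**The case against.** The strongest reply is that nothing in the article says a repeated patient is excluded or has the HU replaced. A reader might infer that the primary analysis discards exactly these patients; the text does not support that. A repeat that the protocol itself permits need not be a deviation, and a patient scanned with the assigned agent has received the assigned intervention. Some wording leans toward the first scan: the endpoint is tied to the three contrast protocols, Myocardial perfusion CT treats the agent used for coronary CT angiography as the randomised one, and Table 2 has a single CT angiography visit. This stands, and it makes the point conditional. It does not settle which scan counts.

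A reader might also blame the complete-case rule ("Because missing values are expected for 5 % or fewer of the participants, we have planned complete-case analysis for the primary analysis") or see a conflict with the 10% dropout allowance. Neither holds. A poorly enhanced scan still yields a measurable, low HU, so it is not missing. Dropout for planning can cover more than missing values, and planning above the expected rate is prudent.

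Per-protocol as the primary noninferiority analysis, with intention-to-treat beside it, is a common design. That is fair in general. Here the departure from assignment would be driven by the outcome and confined to the low-concentration arms, which is where the second set needs a stated role.

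Finally, the calculation assumes that exactly the lowest values go. The actual trigger is a reading judgement with no HU cut-off, and imperfect selection would shrink the shift.

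An article may leave the definition of analysis sets to a fuller document. What this article does fix is the one-sided repeat rule together with a per-protocol decision, and that combination needs an explicit safeguard.

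**Conclusion.** The concern holds as a conditional one. The plan opens a route by which the poorest low-concentration results could leave the primary comparison, and the text shown does not close it. It is not established that the analysis is biased.

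The possible size runs from about 3 HU and a 1.4% error (1% dropped) to 23 HU and 16.5% (10% dropped), against 0.83% with no removal; replacement gives slightly more. These figures rest on a normal model, SD 118.93, 95 evaluable per arm, removal of the lowest values in one arm, and a repeat rate the document does not give. If high-arm enhancement is near 570 HU, the effect is likely to be small. If the low-arm mean is near 388.7 HU and many scans are repeated, it could take up half the margin or more (27/51.26 = 53%).

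Because the direction favours the trial's hypothesis and the remedy costs almost nothing, it should be settled before any unblinded analysis. If a fuller protocol or SAP already contains the safeguard, confirming that is enough.

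**What to change.** Add to Primary statistical analysis:

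1. The primary HU is always measured on the first scan with the randomised agent, for every patient scanned, in both the per-protocol and the intention-to-treat sets.
2. A repeat examination is not a reason for per-protocol exclusion, and its HU is never used for the primary endpoint.
3. The noninferiority conclusion must also hold in the intention-to-treat set.
4. The number of repeat examinations is reported by arm.

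The cost is a short paragraph and a flag in the case report form and image upload that separates first from repeat scans. The low-arm mean may come out slightly less favourable. Requiring both sets is somewhat stricter, but with the first scan used in both they should differ little on this account. The clinical rule on repeat examinations is left unchanged.

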## Discussion

The CONCENTRATE study is a prospective, multicenter, noninferiority, randomized trial evaluating the enhancement effect of two low-concentration contrast agents compared with the high-concentration contrast agent recommended for sufficient opacification in coronary CT angiography, according to established guidelines [14].

The accuracy of coronary CT angiography in the diagnosis of coronary artery stenosis is affected by image quality, which is dependent on the CNR. To achieve a high CNR, high-concentration contrast agents are usually recommended and have been widely used in everyday clinical practice as a standard protocol [14]. According to a study that compared two contrast agents with different concentrations (400 mgI/ml vs. 320 mgI/ml), coronary arterial enhancement was higher when the high-concentration contrast agent was used and higher enhancement levels were found to be associated with lower numbers of inadequately visualized segments [11]. However, in another study that compared four different concentrations (370, 350, 320, and 270 mgI/ml), image quality grade was higher with low-concentration contrast agents, although high-concentration contrast agents showed greater vascular enhancement [15]. The fact that heart rate variability was lower with low-concentration contrast agents, which were all iso-osmolar agents, whereas the high-concentration contrast agents were all low-osmolar agents, might partially account for the higher image quality obtained with lower-concentration-contrast agents in this study. The lowest enhancement of 369.1 ± 85.4 HU obtained with the lowest concentration of 270 mgI/ml in this study could be considered adequate because adequate intra-arterial enhancement for coronary CT angiography has been considered to require more than 250 HU according to previous reports [13, 14].

In this regard, an effort to reduce the amount of iodine should be considered to reduce the probability of contrast-induced nephropathy in patients at risk, as long as diagnostic image quality is maintained [16, 17]. When using low-concentration contrast agents, a combination of low tube potential and iterative reconstruction would be helpful for maintaining high vascular enhancement and image quality. A lower tube potential has the advantages of reducing radiation dose and improving image contrast. However, using a lower tube potential reduces X-ray penetration and increases image noise. Iterative reconstruction is a solution for this problem because it improves image quality by reducing image noise. The combination of a lower tube potential and iterative image reconstruction does not result in a deterioration of image quality and diagnostic accuracy [8, 9]. A single center study tested the feasibility of this combination with a low-concentration (270 mgI/ml) contrast agent compared to a high-concentration contrast agent (370 mg iodine/ml) in coronary CT angiography and demonstrated that a low-concentration contrast agent maintained the contrast enhancement without impairing image quality [10]. The CONCENTRATE trial has been designed to validate this finding as a multicenter study to limit possible bias and secure maximum generalizability.

The CONCENTRATE study will determine whether low-concentration contrast agents are able to provide diagnostic image quality on coronary CT angiography. Because the CONCENTRATE trial will only measure the coronary artery lumen and the myocardium in coronary CT angiography, the results of the CONCENTRATE trial should be further validated for other applications of cardiac CT, including in the evaluation of plaque, in-stent restenosis, and image-based fractional flow reserve. With expanding options for technology, such as feasibly scanning with 70 kVp, and more sophisticated iterative reconstruction methods, CT protocols should be further optimized to apply the results of the CONCENTRATE trial in the real world.

## Trial status

Recruitment commenced in July 2015.

## Abbreviations

AHA, American Heart Association; BMI, body mass index; CAD, coronary artery disease; CNR, contrast-to-noise ratio; CT, computed tomography; ECG, electrocardiography; HU, Hounsfield Unit; ICA, invasive coronary angiography; SNR, signal-to-noise ratio
